### Patient involvement

2.7

Two patient-researchers, members of the Dutch Parkinson Patient Association were consulted in several online meetings to discuss the project idea and research protocol. In particular, their input was sought specifically on the comprehensibility of the patient information, the questionnaires, the Bladder Behavior Information Form, and the PFME.

In addition, feedback from the treatment of 15 patients, according to the treatment protocol, in earlier stages was also consequently incorporated. The eight treatment sessions and electrical stimulation were both well received and tolerated.

## Study outcomes

3

### Primary outcome

3.1

The effect of ES combined with PFME and biofeedback will be evaluated based on LUTS symptoms and the change in IPSS score from baseline (T0) at 12 weeks (T1) across the 3 study arms.

Secondary outcomes involve of incontinence (ICIQ-UI SF; quality of life (ICIQ-LUTSqol and ICIQ-OAB), 24 bladder diary), PFM function, including palpation per vaginum/anum and EMG assessment (Table 1).

### Sample size calculation and statistical analysis

3.2

Given the limited available evidence, the sample size calculation is based on the minimal clinically important difference (MID) of the IPSS-score on LUTS, as estimated in previous studies. Ruffion et al. [42] estimated a MID of 3 points with a standard deviation of 4 in men, while Blanker et al. [43] reported an MID of 5.2 with a standard deviation of 6.7 in men. However, to the best of our current knowledge, there are no estimated MIDs available for women or for conservative therapy.

In PD the IPSS is often used and appears to show a higher score than healthy controls [6,49]. In a recent study, including PD patients with self-reported LUTS the mean score was 13.5 [31].

To study the effect of ES, combined with PFME and biofeedback, for each of the two interventions compared to sham ES and given the expected effect of PFME, a MID of 4.2 will be used and a SD of 6.7 per group is expected.

In our study we will study the effectiveness of ES making two comparisons:

Comparison 1: group 1 (small phase duration) versus group 3 (sham ES) and.

Comparison 2: group 2 (broad phase duration) versus group 3 (sham ES).

In a secondary analysis we also want to compare group 1 against group 2.

Given this 3-arm design, Dunnett's closed testing procedure is used, therewith correcting for multiple testing [50]. This entails that first looking at the test statistics belonging to the two contrasts of main interest [1] vs [2,3] vs [3]. The maximum test statistic of these two will be tested against the critical value belonging to Dunnett's procedure. If this overall/gatekeeping test is rejected, the remaining two contrasts can be tested against regular critical values matching two-sided alpha = 0.05. If the maximum test statistic does not lead to rejection, this implies none of the contrasts are rejected.

The overall power of detecting a MID of 4.2 for at least one of the main comparisons [1] vs [2,3] vs [3] was assessed using Monte Carlo simulation.

Group sizes of 40, 40 and 40, achieved 84 % power for detecting any difference (so either [1] vs [3] or [2] vs [3] or both) and 66 % power for detecting both differences [1] vs [2,3] vs [3] assuming an alternative hypothesis of a mean difference of 4.2 between [1] vs [3] and same difference between [2] vs [3].

Given that the study will be considered successful if at least one effective intervention is found, this achievable power was considered satisfactory.

Regarding attrition, we estimate a loss-to-follow-up of 20 %. Therefore, with 40 participants per group needed in the analysis, 150 participants will be recruited (50 per group).

The primary analysis will use linear mixed models, which accounts for missingness due to study drop-out, under the assumption of missing at random (MAR). Other missing data will be imputed using multiple imputation for intention-to-treat analysis if more than 5 % is missing, with the number of imputations based on the percentage of incomplete patients and relevant variables.

### Data management and data protection

3.3

After inclusion, all data will be stored in a secure, online database system (www.castoredc.com). Every participant is given a unique identifying trial number. The key to the sequential participant code (a combination of country, institute code, study code and sequential participant number) to the participant data is safeguarded by LUMC.

The handling of the data complies with the EU General Data Protection Regulation and the Dutch Act on Implementation of the General Data Protection Regulation. (in Dutch: Uitvoeringswet AVG, UAVG).

The project leader and PI will have access to the complete database, as well as a monitor of the internal monitor pool of the LUMC and the “Health and Youth Care Inspectorate”.

LUMC data management guidelines will be followed and we strive to make our data FAIR (Findable, Accessible, Interoperable and Reusable) as described in a data management plan.

The data sets will be accessible in agreement with the given informed consents and other agreements in place. Data will be made (publicly) accessible following the funder's guidelines.

The data collected for the trial will consist of baseline characteristics, questionnaires, PFM assessment and EMG assessment (Table 1).

### Data safety monitoring

3.4

Monitoring will be executed by (internal) monitors of the LUMC according to the monitor plan. Due to the “low risk trial” character of the study no Data Safety Monitoring Board, no formal stopping rules for the trial and no interim analyses are needed.

## Harms

4

This study is considered to be a low risk trial. The risk of occurrence of side-effects is low [[51], [52], [53]].

Adverse events (AE's) are defined as any undesirable experience occurring to a subject during the study, related to EMG measurement and treatment (biofeedback and ES) with an anal or vaginal probe. Only study related AE's reported spontaneously by the subject or observed by the investigator or his staff will be recorded.

Due to the intervention, hardly any serious AE's (SAEs) are to be expected. Only study related (S)AE's, suspected unexpected serious adverse, will be reported. This means all (S)AE's related to participation in this study protocol, meaning from PFM assessment, EMG assessment, biofeedback and ES treatment. All other (S)AE's will not be reported, as no participant benefit is expected from this.

The sponsor will report the SAE's through the web portal *ToetsingOnline* to the accredited METC that approved the protocol.

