### Intervention and blinding

2.6

The intervention consists of eight protocol-based treatment sessions of 30 min each over a period of 10–12 week. The protocol consists, for all participants, of bladder training [22], biofeedback assisted PFME, MVC's and endurance contractions according to the (dys)function of the PFM and the ability of the individual participant. It also includes relaxation and coordination exercises of the PFM combined with abdominal breathing. Visual feedback of the EMG signals with verbal instruction and reinforcement will be used to teach participants how to control the PFM and how to use the PFM for urge suppression techniques.

For urge suppression, the mean of the peak values of the 10 MVCs obtained during the EMG assessment is used. Half of this mean is displayed as a reference red, top line on the screen, providing visual feedback to both the participant and the therapist. Another red, bottom line, representing the mean baseline muscle activity from the EMG assessment, is used for relaxation. During the intervention, the red line will be adjusted in case of increasing PFM activity in MVC's and decreasing activity in case of more relaxation.

ES will be applied for 20 min, in six therapy sessions.

Participants will have to exercise (approximately 10 min per day) at home in between sessions and learn to integrate the techniques in case of UU and into their daily activities.

Participants are blinded for the treatment, but blinding is impossible for the A- and L-PPT's. Data analysis is conducted by both researcher and statistician, with the statistician being fully blinded.

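### Recording only passively captured events already judged study-related, with therapists who know the arm, is likely to understate harms and leaves arm comparisons open to ascertainment bias

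*Protocol article*

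**What the plan says.** Section 4 (Harms) of the protocol article defines an adverse event as an undesirable experience during the study that is "related to EMG measurement and treatment (biofeedback and ES) with an anal or vaginal probe". It then sets the recording rule: "Only study related AE's reported spontaneously by the subject or observed by the investigator or his staff will be recorded". It closes the rest off: "All other (S)AE's will not be reported, as no participant benefit is expected from this". Reportable serious events go from the sponsor to the ethics committee.

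Section 2.6 (Intervention and blinding) states: "Participants are blinded for the treatment, but blinding is impossible for the A- and L-PPT's". The L-PPTs deliver the eight treatment sessions, and the A-PPTs carry out the assessments at T0 and T1 (sections 2.5 and 2.6).

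The article does not say who decides whether an event is study-related, or whether that person knows the arm. It names no harms outcome and plans no comparison of harms between arms. Table 1 and the data list in section 3.3 contain no adverse-event item.

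**The concern.** Relatedness is normally a judgement attached to an event after it has been recorded. Here it decides whether the event enters the data at all. An event that is not volunteered, not noticed, or noticed but put down to Parkinson's disease leaves no record, and no later analysis can recover it.

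The setting makes this matter more. The therapists who see participants at each session know which stimulation was given. The Discussion (section 6) explains that the sham settings were chosen so as to have little effect. A therapist who knows that a participant is on sham therefore has some reason not to link an event to the stimulation. If that happens, the threshold for recording differs by arm.

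At stake is any tolerability statement the trial will support. Section 1 describes stimulation as well tolerated on the basis of the general population, and section 6 presents the trial as the first of its kind in Parkinson's disease. Its harms data will be read as evidence for this population, in which symptoms are easily attributed to the underlying disease. The efficacy analysis is not affected.

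**Working it through.** **Step 1. Is this a rule on recording or only on expedited reporting?** Section 4 contains both. The sentence in "Only study related AE's reported spontaneously by the subject or observed by the investigator or his staff will be recorded" governs what is recorded, and "All other (S)AE's will not be reported, as no participant benefit is expected from this" governs what is reported. Restricting expedited reports to related events would be unremarkable if everything were recorded. The first sentence removes that possibility. Nothing elsewhere in the article restores it. The absence of an adverse-event item from Table 1 and section 3.3 fits this reading but adds little, since a condensed article may leave forms to the full protocol.

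**Step 2. Inputs for size.** The plan states no adverse-event rate, so it has no harms figure to reproduce. Group size comes from section 3.2: 40 / (1 − 0.20) = 50 recruited per arm. The true rates and capture probabilities below are assumptions.

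Let p be the true event rate in an arm and c the probability that an event is volunteered or noticed and also called study-related. Then

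- recorded rate = p × c
- recorded risk ratio = (p_active × c_active) / (p_sham × c_sham)

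**Step 3. Equal true rates, unequal capture.** The true rate cancels, so the ratio is c_active / c_sham:

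| Capture, active | Capture, sham | Recorded risk ratio (true value 1.0) |
|---|---|---|
| 60% | 60% | 1.0 |
| 60% | 50% | 1.2 |
| 60% | 40% | 1.5 |
| 60% | 30% | 2.0 |

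At a true rate of 20% in both arms, the last row records 0.20 × 0.60 = 12% against 0.20 × 0.30 = 6%. That is 6 against 3 participants out of 50.

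**Step 4. A real excess hidden.** Take true rates of 20% active and 10% sham, with capture of 30% and 60%. The recorded rates are 0.20 × 0.30 = 6% and 0.10 × 0.60 = 6%, so a true ratio of 2.0 is recorded as 1.0.

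**Step 5. Equal capture.** With 60% in both arms, 20% against 10% becomes 12% against 6%. The ratio stays at 2.0, while the difference falls from 10 to 6 percentage points. Bias in the ratio therefore needs capture to differ by arm. Understatement of absolute figures needs only incomplete capture.

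**The case against.** Much can be said for the plan, and some tempting stronger readings do not stand.

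- **Reports from participants only.** A reader might infer that only spontaneous reports count. The rule also covers events observed by the investigator or staff. That second route does not remove the problem, because the therapists who are in a position to observe are unblinded.
- **No unbiased comparison is possible.** The documents do not support this. Participants, who supply the spontaneous reports, are blinded. All arms receive a probe, EMG, biofeedback and some current. Step 5 shows that equal capture preserves the ratio. The article also does not say that therapists decide on relatedness; it leaves open who does. The plan permits differential capture but does not make it certain.
- **The treatment is promoted on its harms profile.** The remark in section 1 about an absence of side effects concerns bladder training and biofeedback-assisted exercises, which all arms receive. No contrast between arms rests on it.
- **No DSMB, so an excess goes unseen.** Section 3.4 says "no Data Safety Monitoring Board, no formal stopping rules for the trial and no interim analyses are needed", on grounds of low risk. A board could not find events that were never recorded, and its absence does not prevent tabulation of those that were. This adds nothing to the point.
- **Unexpected harm is undetectable.** Urinary worsening is measured in every arm whatever its cause, through the IPSS, the ICIQ questionnaires, the bladder diary and the GPE. Infections and falls are not covered in this way.
- **Zero-event limits.** The one-sided 95% upper limit with no events is 1 − 0.05^(1/50) = 5.8% (7.2% with 40). It assumes complete capture and reflects sample size, so it does not measure this flaw.

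What stands of the objection is that the plan claims no harms comparison and the trial is of low expected risk. That limits the weight of the point. It does not change the fact that the recording rule filters events by attribution.

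**Conclusion.** The point holds in a limited form. The article fixes a rule under which harms data are passively collected and filtered on relatedness before recording, in a trial where both therapist groups know the arm and no blinded judge of relatedness is named. Two consequences follow without a numerical assumption: events considered unrelated are lost, and the rate of all events is understated. Recorded rates of truly related events are also likely to be too low, wherever such events go unmentioned or are attributed to another cause.

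The third consequence is conditional. Between-arm figures are biased only if capture differs by arm. Under the assumed capture probabilities the false risk ratio runs from 1.2 to 2.0, and a real doubling can vanish. These figures show what the rule allows; they do not estimate what will happen. The power and sample size are untouched. The change should be made because unrecorded events may not be recoverable later.

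**What to change.** Amend section 4 so that:

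1. every adverse event and serious adverse event from T0 to T1 is recorded in all three arms, whatever its suspected cause;
2. events are elicited with one identical open question at existing contacts, at least at T1 and at the treatment sessions where feasible;
3. relatedness is stored as a separate field. If a team member already blinded to arm can judge it, use that person; no new adjudicator is needed;
4. all events and related events are tabulated by arm.

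Expedited reporting to the ethics committee can stay as approved.

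**Cost.** A small amendment and modest data entry. Asking at T1 alone means up to 150 answers. Asking at all eight sessions adds up to 8 × 150 = 1,200, and the article does not show that the L-PPTs enter data in Castor, so a route for those answers would be needed. No visits are added.

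**Timing.** The trial status section gives recruitment from September 2023 to about mid-2025. A change partway would mix two methods of ascertainment, so report its date and tabulate the periods separately. Blocked 1:1:1 allocation should spread the change roughly evenly over the arms. If recruitment is too far advanced, state the limitation and make no comparative safety claim.

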## Ethical approval and dissemination

5

The study protocol has been approved by the Medical Ethics Review Committee of the Leiden University Medical Center (P22.009).

Dissemination meetings are arranged with the research team (authors) and the A-PPT's.

## Discussion

6

To our knowledge, this is the first RCT evaluating conservative therapy for LUTS in PD. Despite the significant impact of LUTS on QoL, evidence-based interventions for LUTS in PD are limited and needed.

This RCT examines the efficacy of intra-vaginal and intra-anal ES with varying parameters, to reduce UU, frequency and UUI, in conjunction with bladder training and PFME with biofeedback. If this intervention proves effective, it could significantly improve the QoL of PD patients experiencing LUTS. Furthermore, this standard care treatment is readily accessible for all PD patients.

The selection of study parameters is only moderately supported by evidence. A wide range of parameters are used in scientific research. The frequencies employed typically fall within a narrow range of 2–20 Hz. The 20 Hz frequency combined with a 200 μs pulse duration is commonly used in PTNS/TTNS therapies. An 8 Hz frequency with a phase duration of 1000 μs has been used in a previous study [52]. Both 200 μs and 1000 μs pulse durations are at the extremes of the spectrum of phase durations that are typically used. The Sham ES uses a frequency of 100 Hz, which is not expected to have an effect on the UU. Additionally, stimulation is applied to the dorsal side of the pelvic floor to minimize any potential impact.

During the design of this study, various factors were considered, including time investment and burden for participants, evidence supporting PPT interventions, the feasibility of the treatment protocol by PPT's, and the study methodology.

Representatives from the patients' association, as well as medical specialists, PPT's, and nurses, actively participated in the development of the treatment protocol.

This study has limitations. With six A-PPT's across The Netherlands, the travel distance to the A-PPT's remains too great for some potential participants. Furthermore, there is a discrepancy between the perceived LUTS and the measurable severity of these symptoms. To the best of our knowledge, there is no clear cutoff point in LUTS questionnaires, which affects the inclusion of participants and may introduce bias.

Should this study demonstrate that ES combined with PFME and biofeedback is effective, a new conservative treatment option for LUTS in PD would be available that is also easily accessible for patients.

## Trial registration

Registered at clinicaltrials.gov (Trial registration: NCT05814614 Date of registration:/First Posted: 18-04-2023.

## Trial status

Recruitment started at September 2023, the estimated end date of the last recruitment is august/medio 2025.

